#### Analysis of Dose Effects

Dose effect will be analyzed with unconditional and conditional growth models to estimate and model the changes in behavioral and brain outcomes as training progresses.

#### Analysis of Age Differences

After ensuring that the 3 training groups are equivalent, we will first assess the effect of age prior to intervention using ANOVAs, which will compare the performance in both age groups at baseline to assess whether the intervention reduces the effect of age on behavioral and brain outcomes. Separate analyses will be used for the different outcome variables. Using additional ANOVAs, we will then compare the performance of younger participants to the POST4 performance of older participants as a function of their training group and task conditions. Performance of each training group will be compared to the younger group using pairwise comparisons. Finally, whole-brain T-tests in SPM12 will compare age groups at PRE and POST4 to observe differences in activation patterns.

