### Study Population and Eligibility Criteria

A total of 90 community-dwelling older adults (age 60-85) and 30 younger adults (age 20-35) were enrolled in the study. Older adults and younger adults were recruited in the Montreal area through advertisements in community centers, associations, local newspapers, and CRIUGM’s participants registry (*Banque de participants du*
*CRIUGM*). In addition, students, who were enrolled in an undergraduate laboratory course and wished to help with the study recruited younger adults among their acquaintances. Younger and older adults with similar educational levels were recruited in order to reduce the cohort effect on education.

Participants with the following criteria were included in the study: right-handed, fluent in French, and sufficient visual and auditory acuity to undergo neuropsychological testing. Participants were only included if they performed above the cut-offs on the delayed recall portion of the Logical Memory Test of the Wechsler Memory Scale for older adults. Performance on the Logical Memory Subtest was considered normal based on the following education-adjusted cut-off scores used in the Alzheimer’s Disease Neuroimaging Initiative (ADNI) study: 9 or more for 16+ years of education; 5 or more for 8-15 years of education; 3 or more for 0-7 years of education [38-40].

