Participants were excluded from the study if they had received a diagnosis of a disease or injury of the central nervous system (ie, moderate to severe chronic static leukoencephalopathy [including previous traumatic injury], multiple sclerosis, neurodevelopmental disorders, subdural hematoma [past or current], subarachnoid hemorrhage, primary cerebral tumor or cerebral metastases, epilepsy, dementia or other neurodegenerative diseases, stroke, intracranial surgery or major surgery within the last 2 months), alcoholism or substance abuse, general anesthesia in the past 6 months, serious comorbid conditions, major depression or anxiety, schizophrenia, or other major psychiatric disorders (eg, bipolar disorder). Participants were also excluded if they were unable to undergo an MRI scan, due to medical contraindications, or tolerate the procedure. Older adult participants were excluded if they reported subjective cognitive decline [41], such as feeling their memory is worse than it used to be and that it worries them, or if they had previously participated in structured attentional control training. Despite the time required for the participants to carry out the study, no change in the habits of daily living was required, except to abstain from cognitive training during the intervention. The younger adults were only included in the study if they were no longer full-time students. This constraint was intended to increase the diversity of age and education in our sample of younger participants in order to better match the diversity of our sample of older subjects. Moreover, it was not possible to determine the final level of education of the students, many of whom were actively involved in training programs that have made them experts in metacognitive strategies.

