### Statistical Analyses

#### Sample Size

Our aim is to recruit 90 participants in total. Given an attrition rate between 10% and 16% (see [54] for a review), there would be approximately 27 participants per condition. Assuming a significance level of α=.05, a power of 0.80, and a correlation of *r*=.50 between 3 repeated measures, the G*Power 3 software for mixed designs estimates that the sample size will provide sufficient power to detect a small to medium effect (*f*=0.15). Indeed, small to medium effect sizes correspond to those observed with similar training programs in the meta-analysis by Lampit et al [55].

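### The baseline age comparison sets 90 older against 30 younger adults in ANOVAs, so unequal spread by age would distort its error bars; at POST4 the same effect is small

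*Protocol article*

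**What the plan says.** Under Analysis of Age Differences, the protocol article first assesses the age effect before training "using ANOVAs, which will compare the performance in both age groups at baseline". It then continues: "Using additional ANOVAs, we will then compare the performance of younger participants to the POST4 performance of older participants". The POST4 analysis splits the older adults by training group, includes task conditions as a factor, and compares each training group with the younger adults pairwise. The section does not say how unequal variances are handled.

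The group sizes are under Study Population and Eligibility Criteria: "A total of 90 community-dwelling older adults (age 60-85) and 30 younger adults (age 20-35) were enrolled in the study". Under Sample Size, the article expects that after attrition "there would be approximately 27 participants per condition". The younger adults are tested once and are not trained (Study Design).

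**The concern.** The standard ANOVA error term is a weighted average of the group variances, with weights close to the group sizes. If the groups are equally large, unequal variances do little harm to a two-group contrast. If one group is three times the size of the other, its variance dominates the average, while the true standard error depends mostly on the smaller group. The reported standard error is then too wide if the larger group is more variable, and too narrow if it is less variable.

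The baseline comparison has this 3:1 layout, and its groups are two populations that nothing forces to have equal spread. Objective 6 asks whether training reduces the age deficit, so the plan sets the baseline result beside the POST4 result. If the SDs differ by age, the two tests carry different true error rates, and part of any contrast between them could come from the error term rather than from training.

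**Working it through.** **Inputs**
- Baseline: 90 older, 30 younger (Study Population and Eligibility Criteria).
- POST4: about 27 per training arm (Sample Size) and 30 younger.
- Older/younger SD ratio k: not given in the documents. Assumed range 0.67 to 2, with the younger SD set to 1.
- Nominal two-sided level 5%.

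**The plan's own figure.** There is none to reproduce for the age comparison. The Sample Size statement ("Assuming a significance level of α=.05, a power of 0.80") goes with "a correlation of *r*=.50 between 3 repeated measures". It therefore describes the training design and not a contrast with younger adults measured once.

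**Pooled over true standard error**

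Baseline, two groups:
sqrt{[(89k² + 29)/118] × (1/90 + 1/30)} / sqrt(k²/90 + 1/30)

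For k = 1.5 the pooled variance is (200.25 + 29)/118 = 1.943. The pooled SE is sqrt(1.943 × 0.04444) = 0.2939, the true SE is sqrt(0.0250 + 0.0333) = 0.2415, and the ratio is 1.217.

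POST4, one arm against the younger adults, with the error term pooled over all four groups:
sqrt{[(78k² + 29)/107] × (1/27 + 1/30)} / sqrt(k²/27 + 1/30)

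For k = 1.5 the pooled variance is (175.5 + 29)/107 = 1.911. The pooled SE is sqrt(1.911 × 0.07037) = 0.3667, the true SE is sqrt(0.0833 + 0.0333) = 0.3416, and the ratio is 1.074.

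POST4, with only the two compared groups pooled:
sqrt{[(26k² + 29)/55] × (1/27 + 1/30)} / sqrt(k²/27 + 1/30)

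For k = 1.5 the pooled variance is 87.5/55 = 1.591, the pooled SE is 0.3346, and the ratio is 0.980.

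**Results** (sizes simulated with normal data, 40,000 runs per setting)

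| SD ratio k | Baseline 90 v 30: SE ratio, size | POST4, four-group error: SE ratio, size | POST4, pair only: SE ratio, size |
|---|---|---|---|
| 0.67 | 0.82, 10.5% | 0.92, 7.2% | 1.02, 4.5% |
| 1.25 | 1.12, 2.8% | 1.04, 4.0% | 0.99, 5.2% |
| 1.5 | 1.22, 1.8% | 1.07, 3.6% | 0.98, 5.7% |
| 2 | 1.37, 0.8% | 1.11, 3.0% | 0.97, 6.0% |

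The Welch test stays close to 5% in every row.

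**Power.** The age gap was set so that a test with the correct standard error has about 80% power. For k = 1.25, 1.5 and 2:
- Baseline: pooled 71%, 65%, 54%; Welch 78%, 79%, 79%. The loss is about 7, 14 and 25 points.
- POST4, four-group error: pooled 77%, 75%, 72%; Welch about 78% throughout. The loss is about 1.5, 3 and 5.5 points.
- Equal SDs: Welch gives up about one point (baseline 79.6% against 78.6%; POST4 78.8% against 78.0%).

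**The case against.** The strongest reply is that the article says only that ANOVAs will be used. A common error variance is the usual meaning of the word but not its stated one, and a condensed article may leave variance handling to an analysis plan. This stands in part. It is why the point is an improvement to a named method and not an error of fact.

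The second reply is that nothing in the documents shows unequal spread. This stands. A reader might take the remark that full-time students were excluded "in order to better match the diversity of our sample of older subjects" as an admission that older adults are more variable. It concerns the mix of ages and education in the younger sample, and describes a step meant to make the groups more alike. Nor are age spans of 25 and 15 years outcome SDs. Hence the calculation covers both directions.

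The third reply concerns POST4. A reader might infer that the 90-to-30 imbalance carries over to POST4, so that a remaining age gap is easily missed, in favour of the hypothesis that trained older adults reach younger levels. The documents do not support this. The POST4 contrasts are by training arm and nearly balanced. Any loss of power there needs both more variable older adults and a four-group error term, and it is then a few points. With pairwise pooling the test becomes slightly liberal instead.

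Finally, this is the last of six objectives, and the primary composites are analysed by mixed models in the randomised arms, which this point does not touch.

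**Conclusion.** The point holds at baseline, conditionally. If one common error variance is used and outcome SDs differ by age, the baseline age-effect standard error is wrong by an amount that matters: 12% to 37% too wide for SD ratios of 1.25 to 2, and about 18% too narrow at 0.67. At POST4 the distortion is small for SD ratios of 1.25 to 2: 4% to 11% too wide with a four-group error term, and 1% to 3% too narrow with pairwise pooling. The consequence is that the two age tests would not be on the same footing when read against each other.

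This rests on the ordinary reading of ANOVA, on assumed SD ratios, on normal data in the simulations, and on 27 per arm at POST4. It does not show that the age conclusions will be biased toward the hypothesis. Whether a non-significant POST4 gap may be read as reaching younger levels is a separate question that no variance correction answers. The point is minor.

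**What to change.** In Analysis of Age Differences, state that the age comparisons will be fitted with a linear or mixed model that allows a separate residual variance for younger and older adults. Such a model also carries the repeated task-conditions factor, which a one-way Welch ANOVA cannot. Use Welch tests for the simple two-group contrasts. Report each older-younger difference, at baseline and at POST4, with its confidence interval from that model or test, so that the two time points can be compared as estimates and not only as significant or not.

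The change takes a sentence or two in the plan and a software option, and needs no new data. It costs about one percentage point of power if the variances are in fact equal.

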### Study Design

The study design presented in Table 1 is a randomized double-blind controlled trial where older participants are randomly assigned to 1 of 3 parallel groups: inhibition, updating, and active control. In line with prior empirical work from our team showing transfer effects following attentional control training in older adults [37], training was provided in 12 30-minute training sessions over 4 weeks. All transfer measurements were completed once by a group of younger adults who did not receive the training. This is used to assess whether training helps increase performance and brain status of older adults to the level of younger adults. Given the large number of appointments, participants were recruited and trained in 5-6 waves. The study was carried out at the Research Center of the Institut universitaire de gériatrie de Montréal (CRIUGM).

**Table 1 table1:** Study design.

Schedule of events			Study period											
			Screening, baseline, and pretest		Intervention	Posttest 1	Intervention	Posttest 2		Intervention	Posttest 3	Intervention	Posttest 4	
Timepoint			V1	V2	V3–V5	V6	V6–V8	V9	V10	V11–V13	V14	V14–V16	V17	V18

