### Procedure

After a first telephone contact to assess global eligibility, potential participants were invited to the laboratory to consent to participate in the study, complete standardized clinical and neuropsychological assessments, and the outcome measurements for the baseline (V1; see list in Table 1). A brain imaging examination for the baseline was completed the following week (V2). Eligible participants were given CAD 50 (~US $38) at each brain imaging session, for a total of CAD 150 (~US $114) for older adults and CAD 50 (~US $38) for younger adults.

Data on proximal cognitive and brain outcomes were collected at 3 timepoints: no more than 2 weeks prior to training for the baseline (PRE), between training sessions 6 and 7 (POST2), and no more than 1 week following the end of training (POST4) for the postbaseline tests. Complex WM outcomes were measured at 5 time points: (1) at PRE; (2) after the third training session (POST1), (3) at POST2, (4) after the ninth training session (POST3), and at (5) POST4. The complex WM outcomes at POST1 and POST3 were completed on the same day as a training session to reduce travel and the number of visits to the laboratory. The standard duration of the study was 8 weeks and involved 18 appointments. Participants were informed that the study must be performed without discontinuity. A postponement of up to 1 week was exceptionally authorized in the event of unforeseen circumstances. To limit the influence of the circadian rhythm on performance, training sessions and assessments were performed at similar times of day (ie, morning or afternoon) for a given participant. In addition, at the end of the first appointment, a personalized calendar containing all dates and durations of appointments was given to each participant in paper format. A reminder email (or a phone call made if no email address was available) was also sent the day before each MRI appointment.

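### Objective 6 rests on separate comparisons of each arm at POST4 with once-tested younger adults; these mix training with retest gain and smaller groups, and no trained-versus-control test of gap closure is tied to them

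*Protocol article*

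**What the plan says.** **Younger group.** Study Design: "All transfer measurements were completed once by a group of younger adults who did not receive the training". The purpose follows: "This is used to assess whether training helps increase performance and brain status of older adults to the level of younger adults".

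**Older group.** Procedure: "Data on proximal cognitive and brain outcomes were collected at 3 timepoints" (PRE, POST2, POST4), and "Complex WM outcomes were measured at 5 time points" (PRE and POST1 to POST4). Table 1 puts the virtual car ride on the five-point schedule.

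**Analysis.** Analysis of Age Differences opens with a check on the training groups ("After ensuring that the 3 training groups are equivalent"). It then uses ANOVAs to "compare the performance in both age groups at baseline to assess whether the intervention reduces the effect of age", with older adults taken as one group. Further ANOVAs follow, in which "we will then compare the performance of younger participants to the POST4 performance of older participants" by training group and task condition. Finally: "Performance of each training group will be compared to the younger group using pairwise comparisons".

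**Interpretation.** Objective 6, the Hypotheses and the Discussion all ask whether training shrinks the age deficit or lifts older adults to the younger level.

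**The concern.** Objective 6 is a causal question about training, but the comparison planned for it changes three things between PRE and POST4. Older adults have been trained. They have also repeated the tests two or four more times, while the younger reference stays at a first attempt. And the older side shrinks from the pooled sample to a single arm.

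Retest gain narrows the observed gap, and a smaller group makes any given gap less likely to be significant. Both push towards the appearance of catching up. The section has no adjustment for repeated testing and no contrast asking whether the gap closed more in a trained arm than in the quiz arm. What remains is a set of separate arm-against-younger results, and a difference in significance between two arms is not a test of the difference between them. At stake is a claim that training restores performance towards younger levels when the trained arms may have gained no more than the quiz arm.

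**Working it through.** **The plan's own figure.** The document gives no power figure for the age comparison. Its one figure, 0.80 for f = 0.15 (Sample Size), concerns the time by training interaction. With λ = f²·N·m/(1−r), m = 3 measures, r = .50 and 3 groups, N = 90 gives λ = 0.0225 × 90 × 3 / 0.5 = 12.15 and power 0.796, so the figure reproduces for the 90 recruited. At N = 81 (27 per arm) λ = 10.94 and power is 0.745. This does not bear on the present point.

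**Inputs from the document.** 90 older and 30 younger adults; about 27 per arm after attrition, so 81 in all; α = .05; r = .50 between repeated measures.

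**Assumptions.** Age gap 0.6 to 1.0 SD and retest gain 0 to 0.5 SD, since the document gives neither; two-sided tests; SD 1; no training effect in any arm.

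**Step 1: group size alone, no retest gain.** Noncentral t with δ = gap / √(1/n₁ + 1/n₂). For a 0.6 SD gap, 81 vs 30 gives 0.6/0.214 = 2.81 and 27 vs 30 gives 0.6/0.265 = 2.26.

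| Gap (SD) | Power, 90 vs 30 | Power, 81 vs 30 | Power, 27 vs 30 |
|---|---|---|---|
| 0.6 | 0.81 | 0.80 | 0.60 |
| 0.8 | 0.96 | 0.96 | 0.84 |
| 1.0 | 0.997 | 0.996 | 0.96 |

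**Step 2: add retest gain.** The POST4 gap becomes gap minus gain. The chance that a given arm does not differ from the younger group, for gains of 0, 0.3 and 0.5 SD, is 16%, 54% and 80% (gap 0.8) or 4%, 26% and 54% (gap 1.0).

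**Step 3: the patterns that could be read as training success.** Simulation, 40,000 runs per row, one shared younger group, PRE-POST4 correlation .50, 27 per arm. Column A: gap significant at PRE, but not at POST4 in at least one of the two trained arms. Column B: as A, and the quiz arm still differs from the younger group. Column C: as A, but a trained arm without a significant gap must also have a significantly larger PRE-to-POST4 change than the quiz arm.

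| Gap | Retest gain | A | B | C |
|---|---|---|---|---|
| 0.6 | 0 | 36% | 22% | 2% |
| 0.6 | 0.2 | 63% | 20% | 3% |
| 0.6 | 0.3 | 71% | 15% | 3% |
| 0.6 | 0.5 | 78% | 5% | 4% |
| 0.8 | 0 | 22% | 16% | 2% |
| 0.8 | 0.2 | 52% | 25% | 3% |
| 0.8 | 0.3 | 67% | 25% | 3% |
| 0.8 | 0.5 | 88% | 16% | 4% |
| 1.0 | 0 | 7% | 6% | 1% |
| 1.0 | 0.2 | 25% | 17% | 2% |
| 1.0 | 0.3 | 40% | 23% | 2% |
| 1.0 | 0.5 | 71% | 25% | 4% |

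B is the relevant column, because the quiz arm is in the plan and would reveal a retest gain common to all arms. It runs from about 5% to 25%.

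**Step 4: what a non-significant POST4 difference can show.** For 27 vs 30 the standard error is √(1/27 + 1/30) = 0.265 SD, so the 95% interval is ±2.004 × 0.265 = ±0.53 SD. A non-significant result is compatible with a remaining gap of half an SD or more.

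**Step 5: the contrast that removes the problem.** Let Y be the younger mean. Gap closure in an arm is (Y − PRE) − (Y − POST4) = POST4 − PRE. Trained minus quiz closure is therefore the difference in change, and Y cancels, as does any retest gain common to both arms. Simulated with no training effect and 27 per arm, this contrast has a false-positive rate of 0.048 to 0.052 for retest gains of 0 to 0.8 SD.

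**The case against.** **The quiz arm is already there.** It is one of the three training levels, has the same number of testings and is also compared with the younger group. This stands, and it is why column A overstates the problem. It does not close the point, because the section names no test between arms and column B remains.

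**The mixed models already test efficacy.** Analysis of Behavioral and Brain Outcomes plans time by training models for the proximal, working memory and virtual reality outcomes, and these can supply the contrast in step 5. A reader would see a null result there beside the age comparison. This also stands; column C shows how far it would help. But Analysis of Age Differences uses separate ANOVAs and does not link Objective 6 to those models.

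**Versions are counterbalanced.** Randomization and Blinding describes a Latin square within each age group. That limits item-specific practice, not familiarity with the task itself.

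**No decision rule is stated.** A reader might infer that a non-significant POST4 difference will be declared parity with younger adults. The document gives a purpose, not a criterion, and an article may leave an interpretation rule to a fuller plan. The point therefore rests on the comparison chosen, not on a rule the authors did not write.

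**The equivalence check.** One might also object to requiring equivalent training groups first. No test is named, and the phrase reads naturally as a check before pooling the arms at PRE. Removing it is a matter of preference.

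**Conclusion.** The concern holds for Objective 6. As planned, the POST4 comparison with younger adults cannot separate training from repeated testing and from the smaller groups, and nothing in that section tests whether trained arms closed the gap more than the quiz arm. With no training effect, a trained arm appears to catch up while the quiz arm does not in roughly 5-25% of trials over the assumed ranges. The true age gap and retest gain are unknown, so this shows a possibility and a range, not an expected amount. With a large gap and no retest gain the problem is small.

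The retest part applies to performance and task fMRI, and hardly to brain structure; the loss of power applies to every outcome. A reader might go further and say that Objective 6 will come out positive whether or not training works. The document does not support that: the quiz arm and the mixed models both offer a check. The primary proximal composites, tested against active control, are unaffected.

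**What to change.** In Analysis of Age Differences:

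1. State that Objective 6 is answered by the trained-minus-quiz difference in PRE-to-POST4 change, for each trained arm. For behavioral outcomes this is the corresponding contrast in the time by training mixed models; for brain outcomes, specify its counterpart.
2. Report it with a confidence interval, set against the PRE gap between older and younger adults.
3. Keep the POST4 comparisons with younger adults as description for all three arms.
4. State that a non-significant difference will not be read as having reached the younger level. Make that claim only if the interval lies within a pre-stated margin.

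**Cost.** A change of analysis wording only; all the data exist. The price is a slightly wider interval and a more modest claim. At r = .50 the SD of change is √(2 × (1 − .50)) = 1, so the contrast has standard error √(2/27) = 0.272 SD and a 95% interval of about ±0.55 SD, against ±0.53 SD for the POST4 comparison. With an assumed 0.8 SD gap that is about ±68% of the gap (0.546/0.8), before allowing for uncertainty in the gap itself.

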#### Analysis of Behavioral and Brain Outcomes

We will use a modified intention-to-treat analysis of behavioral outcomes to minimize attrition-related bias, so that all participants who have completed at least one postbaseline assessment will be analyzed. The effect of training programs on the behavioral outcomes will be analyzed with linear mixed-effects models (LMMs) as this analysis makes it possible to compare performance growth between groups and is resistant to missing values. Training improvements will be tested using IES as the dependent variable with 2 separate analyses using *session* (12 levels: session 1 to session 12) *× condition* (3 levels: IES 1-back/IES 2-back/IES 3-back) for the updating training and *session* (12 levels: session 1 to session 12) *× condition* (2 levels: IES Congruent/IES Incongruent) for inhibition training. When significant interaction effects are found, pairwise comparisons will be computed within each training group (comparing performances at sessions 6 and 12 to session 1) and between training conditions at sessions 6 and 12.

Efficacy of training to improve proximal task performances will be tested at 2 separate *time* (three levels: PRE/POST2/POST4) × *training* (3 levels: inhibition/updating/general knowledge) LMMs, using inhibition and updating composite scores as dependent variables. When significant interaction effects are found, pairwise comparisons will be computed within each training group (comparing performances at POST2 and POST4 to PRE) and between training groups (comparing performances for the inhibition and updating condition to general knowledge condition) at POST2 and POST4. To reduce the statistical power cost due to multiple testing corrections and as we have a priori hypotheses, we will also conduct LMM analyses in the absence of interaction to make a direct comparison between the performances of the general knowledge training group (control active) and the updating or inhibition training groups separately.

Efficacy of training to improve complex WM will be tested in the same way with separate time-varying LMMs (5 levels: PRE/POST1/POST2/POST3/POST4) × *training* (3 levels: inhibition/updating/general knowledge) for each task (ie, reading span, alpha span, and VR composite score).

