#### Analysis of Moderators

Linear and logistic regression analyzes will evaluate the relationship between change scores (from behavioral and brain outcomes) and personal variables. As predictors, we will use: (1) education, (2) cognition at baseline; (3) scores on the CRQ; (4) motivation scale score; (5) sex; (6) genotypes (ie, BDNF, COMT, and APOE-ε4); (7) pretraining intracranial volume and white matter lesions; (8) regional gray matter volumes in the prefrontal and lateral temporal cortices; (9) basal ganglia and hippocampi; and (10) pretraining functional activations in the prefrontal and lateral temporal cortices, basal ganglia, and hippocampi. Linear multiple regression and dichotomous moderator analyzes will also be used to examine whether the CRQ’s score and the genotypes moderate the relationship between the change scores and the other predictors.

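### For behavioural outcomes, the POST4 age comparison drops older adults without a POST4 score while the PRE comparison is not limited to the same people

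*Protocol article*

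**What the plan says.** Under Analysis of Behavioral and Brain Outcomes, the protocol adopts a modified intention-to-treat set for behavioural outcomes so that "all participants who have completed at least one postbaseline assessment will be analyzed". It chooses linear mixed models partly because they cope with missing values. The stated purpose is to limit bias from attrition.

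The Sample Size section expects such attrition. It begins "Our aim is to recruit 90 participants in total", continues "Given an attrition rate between 10% and 16" (per cent), and concludes that "there would be approximately 27 participants per condition".

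Objective 6 asks whether training reduces the age-related deficit. Analysis of Age Differences answers it with a different tool: ANOVAs of younger against older adults at baseline, then additional ANOVAs that "compare the performance of younger participants to the POST4 performance of older participants as a function of their training group", with each training group compared pairwise with the younger group. The younger adults are tested once and are not trained.

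**The concern.** The conclusion on Objective 6 comes from setting two age gaps side by side, one before training and one after. That reading needs both gaps to describe the same older adults. As written, someone who stops after POST2 (or after POST1 or POST3, for the complex working memory tasks) belongs to the behavioural analysis set and can contribute to the PRE ANOVA, but cannot enter the POST4 ANOVA.

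The Hypotheses section expects older adults to rise to the level of younger adults, so a small POST4 gap is the favourable result. If the people who leave tend to be the weaker performers, the gap shrinks through a change of sample alone. This is a stated method that conflicts with the protocol's own reason for choosing mixed models.

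**Working it through.** **Inputs from the protocol.** 90 older adults in three arms; planned attrition 10% to 16%; correlation .50 between repeated measures (Sample Size); 30 younger adults.

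**Inputs assumed, not in the protocol.** No true change from PRE to POST4; dropout depends on the PRE score with an odds ratio of 1.5 to 3 per SD lower; PRE–POST4 correlation r of .5 to .7, the lower end being the protocol's planning value; everyone counted as attrition lacks POST4.

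**Step 1: the plan's own retention figure.** 90 × 0.90 / 3 = 27.0 per arm and 90 × 0.84 / 3 = 25.2 per arm. The stated figure of about 27 reproduces at the 10% end. The number without POST4 is 90 × 0.10 = 9 to 90 × 0.16 = 14.4.

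**Step 2: who enters which analysis.** Take a participant who leaves after POST2. Mixed model: included. PRE ANOVA: included, since no restriction is stated. POST4 ANOVA: not included, because there is no value to enter.

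**Step 3: size of the shift.** Standardise older adults' PRE scores to mean 0 and SD 1. Let d be the dropout proportion and Δ the PRE difference, completers minus dropouts. Since (1 − d) × completer mean + d × dropout mean = 0, the completer PRE mean is d × Δ. With no true change and dropout depending on PRE, the completer POST4 mean is r × d × Δ. Solving the logistic dropout model for each attrition level gives:

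| Attrition | Odds ratio per SD lower | Completer PRE mean (SD) | POST4 shift, r = .5 | POST4 shift, r = .7 |
|---|---|---|---|---|
| 10% | 1.5 | 0.04 | 0.02 | 0.03 |
| 10% | 3 | 0.10 | 0.05 | 0.07 |
| 16% | 1.5 | 0.06 | 0.03 | 0.04 |
| 16% | 3 | 0.15 | 0.08 | 0.11 |

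With an odds ratio of 1 the shift is 0 in every row.

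**Step 4: against the precision of the comparison.** For one arm of about 26 against 30 younger adults, the standard error is √(1/26 + 1/30) = 0.268 SD. The shift therefore runs from 0.020 / 0.268 = 0.07 to 0.105 / 0.268 = 0.39 standard errors.

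**Step 5: check by simulation.** The true age gap was set at 1.00 SD at both visits, with no training effect and 90 older and 30 younger adults. With Δ about 0.5 SD, the POST4 completer gap came out at 0.93 to 0.98 SD. With Δ about 1 SD it was 0.87 to 0.96 SD. These ranges cover r = .5 and r = .8 and both attrition levels. The low end, 0.87, belongs to r = .8 and so lies slightly beyond the table. With non-selective dropout the gap stayed at 1.00.

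**Step 6: would completers at both visits cure it?** Not fully. In the same simulation at 16% attrition, r = .5 and Δ about 1 SD, the completers' gap was 0.843 at PRE and 0.920 at POST4. The sample is now constant, but regression to the mean makes the gap appear to widen.

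**The case against.** Several points on the other side stand. Nothing in the protocol indicates that lower scorers leave more often, and 10% to 16% is a planning range taken from a review, not this trial's loss. The shift is mostly below 0.1 SD. Objective 6 is secondary: the primary proximal outcomes are analysed by mixed model on the modified intention-to-treat set and are untouched. The POST4 comparison is made by training group, so similar selective dropout would also shrink the gap in the active control arm, which partly exposes the artefact. That safeguard is informal, however: the section specifies pairwise comparisons with the younger group, not a change in the age gap relative to control.

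It can also be said that a condensed article leaves missing-data handling to a fuller document. That would answer a complaint about silence. Here the article names the method, and the named method cannot use people whom another section says will be analysed.

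A reader might infer three stronger things that the protocol does not support:

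- **That the moderator analysis loses the same people.** That section will "evaluate the relationship between change scores (from behavioral and brain outcomes) and personal variables" but names no end visit. Under Procedure, postbaseline scores exist at POST2 for proximal and brain outcomes and from POST1 for complex working memory, so some who leave early still have a change score. Genotype comes from saliva taken at V10, and motivation from a telephone call after the study, so early leavers may lack these under any model. The regressions also compare no age groups.
- **That the brain outcomes are affected in the same way.** They are analysed per protocol, so the older sample may already be the same at both visits.
- **That the PRE ANOVA certainly uses all 90.** It may use the modified intention-to-treat set. That set would still contain people without POST4.

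**Conclusion.** The point holds for behavioural outcomes under Objective 6. The POST4 ANOVA excludes older adults without a POST4 score, the PRE ANOVA is not restricted to match, and this is at odds with the population and the reasoning the protocol adopts for the same outcomes. The resulting bias is modest and conditional: about 0.02 to 0.11 SD, at most about 0.4 standard errors for one arm against the younger group. This assumes planned attrition of 10% to 16%, a dropout odds ratio of 1.5 to 3 per SD lower, r of .5 to .7 and no true change. It vanishes if dropout is unrelated to performance. When low scorers leave, it runs towards the hypothesised smaller gap, so it is worth removing, but it does not threaten the primary analysis.

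**What to change.** For behavioural outcomes, estimate the PRE and POST4 means of each training arm from the planned mixed model on the modified intention-to-treat set, and compare both with the younger group's mean. Both age gaps then refer to the same older adults. Keep the completer ANOVA at POST4 as a sensitivity analysis. Limiting both ANOVAs to completers is a weaker alternative, for the reason shown in step 6.

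The cost is a change of wording in Analysis of Age Differences and a little extra analysis. The models are already planned and no new data are needed. The price is reliance on data being missing at random, which the planned mixed models already accept.
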